# Protocol for a multi-site, cluster‐randomized, phase III, comparative clinical trial of geriatric assessment of older patients with non‐small‐cell lung cancer: the ENSURE-GA study

**DOI:** 10.1186/s12877-021-02028-w

**Published:** 2021-01-22

**Keywords:** Geriatric assessment, Lung cancer, Cluster‐randomized trial, Cancer treatment, Patient satisfaction

## Abstract

**Background:**

In Japan, approximately half of all lung cancer patients are aged > 75 years, and the proportion of older patients is increasing. In older patients, it is necessary to consider comorbidities and concomitant drug use to ensure optimal cancer treatment; however, geriatric assessment (GA) is not widely performed. We plan to conduct a study (ENSURE-GA) of GA in older lung cancer patients to determine whether GA with intervention improves patient satisfaction with their treatment.

**Methods:**

The study will be a phase III comparative clinical trial with a cluster-randomized design, and it will be conducted at 81 sites distributed throughout Japan. Approximately 1000 lung cancer patients aged ≥ 75 years will be enrolled in the study. All participants will undergo a standardized GA before starting treatment (using an iPad). At the intervention sites, the GA results and intervention method recommended on the basis of the GA results will be returned as an instant report to guide the physician’s choice of intervention. At the control sites, the physician will decide on interventions based on standard practice. All participants will complete a patient satisfaction survey before treatment initiation (after the GA) and 3 months later.

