## Methods

### Study objective, design, and setting

The primary objective of the ENSURE-GA study is to evaluate the effect of an intervention based on a standardized GA on patient satisfaction with their treatment. This study will be a phase III comparative clinical trial with a cluster-randomized design and will be conducted in 81 medical facilities that have been selected based on the following four factors: (i) number of beds ( ≧ 200 beds or < 200 beds); (ii) whether or not designated as a cancer hospital by the Japanese Ministry of Health, Labor, and Welfare; (iii) region (divided into 6 regions, and these regions were evenly allocated with participating facilities from each region); and (iv) whether GA is usually included in medical treatment. Each facility will be randomly allocated in order of enrollment to the intervention or non-intervention group in a 1:1 ratio.

The primary endpoint will be the change in patient satisfaction according to the Health Care Communication Questionnaire (HCCQ) questionnaire between the GA and 3 months later. The secondary endpoints will be (i) the change in the quality of life; (ii) the treatment completion rate; (iii) the proportion of participants showing improvement by at least one grade in their Eastern Cooperative Oncology Group performance status (ECOG-PS); (iv) the relationship between the pre-chemotherapy risk assessment results and adverse events, evaluated separately for cytotoxic anticancer agents, molecular-targeted agents, and immune checkpoint inhibitors; and (v) the proportion of screened patients who had vulnerability factors in at least one of the GA tools and are enrolled in the study.

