We have built a GA tool as an iPad application and have developed a system that displays GA results and recommendations for related interventions. Using this system, GA is performed for each participant. In the intervention facilities, participants’ GA results and the intervention method recommended on the basis of these results will be displayed immediately on the iPad in the form of a report. Using this report, the responsible physician will explain the GA results and the intervention method to the participant (Table 1). In the non-intervention facilities, the physician will perform a GA, but the results and the intervention method recommended based on these results will not be displayed on the iPad. The physician will decide on treatment solely on the basis of the ECOG-PS and multiple-organ function, as is currently the standard for lung cancer treatment in Japan. Patients who are analyzed for the primary endpoint are those with one or more vulnerability factors identified using the GA tools. All participants will complete a patient satisfaction survey before treatment initiation and 3 months later (Fig. 1). The ENSURE-GA study is an intergroup trial, and the North East Japan Study Group and CS-Lung are working together to conduct the trial.

**Table 1 Tab1:** Geriatric assessment tools and examples of possible interventions based on the assessment results

Evaluated items	Recommended GA tools	Example of intervention (support) method based on the GA results
Physical function: Falls	• Lawton IADL • “How many times have you fallen during the last 6 months?”	• Referral to an occupational therapist and/or physiotherapist • Prevention of falls • Evaluation of safety of home and garden
Complications, polypharmacy	• CCI • Number of drugs in regular use	• Encouraging involvement of family members in management of complications • Collaboration between the primary-care physician and a geriatrician • Consulting a pharmacist regarding reducing the number of medications
Cognitive function	• Mini-Cog	• Evaluation of decision-making capability • Selection of someone with power of attorney, if necessary • Collaboration between a geriatrician and a cognitive function specialist • Prevention of delusions, by adjusting medication
Depressive state	• GDS	• Referral to a psychiatrist • Promoting participation in social activities • Prescription of an antidepressant
Nutrition	• BMI below 21 kg/m^2^	• Referral to a dietician • Provision of support for preparing meals

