## Sample size

For calculating the required number of subjects, first, the number needed for randomization of individual subjects will be calculated, followed by the number needed for cluster randomization. With reference to a report by Mohile et al. [6], it is predicted that the mean scores in the HCCQ Patient Satisfaction Survey before chemotherapy will be 23.3 and 22.2 in the intervention and non-intervention groups, respectively. Considering the common standard deviation for this variable to be 4.5, the two-sided α error to be 5 %, and the detection power to be 80 %, the required number of subjects is calculated to be 526.

Taking the required number of subjects for separate randomization to be *n*, the required number for cluster randomization to be *n’*, the cluster size to be *m*, and the intra-cluster correlation coefficient to be *ρ*, the formula is as follows:
$$n' = ([m - 1] \rho + 1) n$$

Using the above formula, taking *n* to be 526, *m* to be 15, and *ρ* to be 0.05 yields a value of 895 for *n’*, and a required number of clusters of 60; therefore, the number of study sites has been set at a minimum of 60. We assumed that 10 % of prospective participants would have at least one exclusion criterion, and thus the minimum number of participants required is 985.

In addition, in a previous study by our research group, it was found that, among lung cancer patients aged over 75 years, 97 % showed at least one vulnerability factor (unpublished data). Taking this into consideration, the sample size has been set at 1020. Eighty-one medical facilities (study sites) distributed throughout Japan have been selected for the study. We aim to enroll 15 participants per site.

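### The first HCCQ, subtracted in the primary endpoint, may be collected after the intervention has begun, and the sample size is built on a pre-treatment difference rather than on the change

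*Protocol article*

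**What the plan says.** **Timing of the first survey.** The Abstract (Methods) says: "All participants will complete a patient satisfaction survey before treatment initiation (after the GA) and 3 months later". The corresponding sentence under Study objective, design, and setting places the survey before treatment but does not repeat its position relative to the GA.

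**Timing of the intervention.** According to the Abstract, the GA results and recommendations at intervention sites "will be returned as an instant report to guide the physician’s choice of intervention". The main text says that they "will be displayed immediately on the iPad in the form of a report", and continues: "Using this report, the responsible physician will explain the GA results and the intervention method to the participant". At non-intervention sites a GA is done, but "the results and the intervention method recommended based on these results will not be displayed on the iPad".

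**Primary endpoint.** Study objective, design, and setting defines it as the change in satisfaction on the HCCQ "questionnaire between the GA and 3 months later". The Outcome section gives the starting point only as the pre-treatment assessment.

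**Planned effect.** Under Sample size, "it is predicted that the mean scores in the HCCQ Patient Satisfaction Survey before chemotherapy will be 23.3 and 22.2"; the higher mean belongs to the intervention arm, and the common SD is 4.5.

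**The concern.** A baseline for a change score should be taken before the arms are treated differently. Here they diverge when the report is released and explained, which happens in one arm only. The first HCCQ is fixed to a window that opens after the GA and closes at the start of treatment, and the physician's explanation can fall in the same window. The HCCQ measures health care communication, and an explanation of GA results is communication, so the first score could respond to it directly.

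Two things are at stake. First, if part of a lasting benefit is present at the first survey, the change score subtracts it and the trial loses power. If an early benefit fades by 3 months, the expected difference in change is negative and a helpful intervention could look harmful. Second, the sample size is justified by a between-arm difference in pre-treatment scores, which is not the quantity that the primary endpoint compares. This second problem exists whatever the order of survey and explanation at the sites.

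**Working it through.** **Inputs from the article (Sample size section):** means 23.3 and 22.2, so a difference of 1.1; SD 4.5; two-sided alpha 5%; power 80%; cluster size 15; intra-cluster correlation 0.05.

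**The plan's own figures**
- Individual randomisation: 2 × (1.96 + 0.842)² × 4.5² / 1.1² gives 263 per arm, 526 in total. This matches the article.
- Design effect: 1 + 14 × 0.05 = 1.70. 526 × 1.70 = 894.2, rounded up to 895; 895 / 15 = 59.7, so 60 clusters. Both match.

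**Assumptions added here, not in the article**
- A lasting effect of 1.1 points at 3 months, of which a share f is already present at the first survey.
- A correlation r between the two surveys. With SD 4.5 at each survey, the SD of the change is 4.5 × √(2(1 − r)): 5.32 for r = 0.3, 4.50 for r = 0.5 and 3.49 for r = 0.7. Using 4.5 for the change is therefore the same as assuming r = 0.5.

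**Expected difference in change:** 1.1 − 1.1f = 1.1(1 − f).

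**Standard error with SD 4.5:** the effective number is 895 / 1.7 = 526.5, and 4.5 × √(4 / 526.5) = 0.392.

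**Power:** Φ(1.1(1 − f) / 0.392 − 1.96), plus the lower tail where it matters.

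| f | Expected difference | Power (r = 0.5) |
|---|---|---|
| 0 | 1.10 | 80% |
| 0.25 | 0.825 | 56% |
| 0.5 | 0.55 | 29% |
| 1 | 0 | 5% (the type I error rate) |

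At f = 0.5, power is 22% for r = 0.3 and 44% for r = 0.7. To restore 80% power with r = 0.5, the clustered sample size would be 1592 at f = 0.25 and 3574 at f = 0.5. At f = 1 no sample size would do, because the expected difference is zero.

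**Fading benefit (illustration):** with 1.1 points at the first survey and 0.55 at 3 months, the expected difference in change is 0.55 − 1.1 = −0.55.

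**Sample size against endpoint.** The 23.3 and 22.2 are worded as pre-chemotherapy means in the two arms. Read literally, they describe the window of the first survey, and a difference of that size lasting to 3 months would give a difference in change of 1.1 − 1.1 = 0. If they describe something else, the article gives neither the expected difference in change nor the SD of the change.

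**The case against.** The strongest objection is that the deciding fact is not in the article. The harm needs the first HCCQ to follow the physician's explanation, and no sentence says that it does. A report on a screen has not yet reached the patient. A patient who finishes the GA, fills in the HCCQ and then sees the physician fits every statement quoted above. The flowchart is not shown, and the full protocol may give the order. This stands, and it makes the power loss conditional. It does not remove the point, because the one order that the article states (survey after the GA) leaves the unsafe sequence open.

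A reader might infer that the baseline is certainly contaminated, that the change score must subtract the effect, or that the primary endpoint cannot answer the objective. The documents do not support any of these. Full effect at the first survey (f = 1) is also an extreme case: many of the Table 1 interventions are referrals and support measures whose benefit would come later.

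The pre-chemotherapy means are taken with reference to a cited study, so the time point may simply have been carried over from it. They therefore do not show when patients in this trial hear their results. The mismatch with the endpoint remains even so.

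The mixed-effects model might adjust for the first score instead of subtracting it. That helps only in part: with r = 0.5 and f = 0.5, the expected adjusted difference is about 1.1 × (1 − 0.5 × 0.5) = 0.825, still below 1.1.

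**Conclusion.** The point holds in conditional form. As written, the article permits a first HCCQ taken after the intervention has begun and uses that score as the starting point of its only primary endpoint. Separately, and without any condition, the sample size rests on a pre-treatment difference and not on the difference in change to 3 months.

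The size of the first problem depends on f, which the documents do not give. Power is 80% if nothing is present at the first survey, about 56% at f = 0.25, 29% at f = 0.5 (22% to 44% for correlations of 0.3 to 0.7) and 5% at f = 1. These figures assume a lasting 1.1-point effect and, except for the range in brackets, a change SD of 4.5. If sites take the survey before the explanation, little is lost and the correction is one of wording.

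**What to change.** 1. State that in both arms the baseline HCCQ is completed before the GA, or at the latest before the report is released or explained. Use the same starting point in the Abstract, the endpoint definition and the Outcome section. A survey after the explanation can be kept as a separate pre-treatment time point, but not as the baseline.
2. Restate the sample-size assumption for the endpoint actually analysed: time point, expected between-arm difference, and SD of that quantity. If the change is kept, give the correlation or the SD of the change.
3. For patients already surveyed after the explanation, add a sensitivity analysis that compares 3-month HCCQ scores in the mixed model and neither subtracts nor adjusts for the first score. Specify it before outcome data by arm are examined.

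**Cost.** Items 1 and 2 need a few sentences in the protocol and a fixed order of procedures at sites, with no extra visit. Restating the assumptions could show that a different number of patients is needed. Item 3 has a real downside: it gives up the precision that a baseline score can add, and it does not correct imbalance that can arise when patients are enrolled at facilities whose arm is already allocated. That is why it is proposed as a sensitivity analysis and not as a replacement for the primary analysis.

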**Discussion:**

The purpose of the ENSURE-GA study is to evaluate whether GA with interventions improves patient satisfaction with treatment outcomes. The study may lead to the increased use of GA and improved treatment of cancer in older adults. The results will also be used to prepare guidelines for treating older cancer patients and will provide a foundation for the development of a standardized geriatric oncology system.

**Trial registration:**

The study has been registered in the University Hospital Medical Information Network database (no. UMIN000037590). The registration date is August 4, 2019, and the protocol version is 2.0. (https://upload.umin.ac.jp/cgi-open-bin/ctr/ctr_view.cgi?recptno=R000042853.)

## Background

Aging is a global phenomenon among patients with cancer. According to the National Cancer Center Information Service, people aged > 65 years currently account for 73 % of the total patients with cancer, and this proportion continues to increase, especially in Japan, which is particularly important. In 2015, among males, 79 % of patients with lung cancer were aged > 65 years and 48 % were aged > 75 years, while among females, 78 % of patients with lung cancer were aged > 65 years and 50 % were aged > 75 years. Older cancer patients are diverse; thus, in conjunction with their primary treatment, supportive and palliative treatments should be provided based on the results of a geriatric assessment (GA). The GA should evaluate aging-related deterioration in physiological function, comorbidities, and polypharmacy to ensure safe and effective chemotherapy.

In 2018, the American Society of Clinical Oncology published the article “Practical Assessment and Management of Vulnerabilities in Older Patients Receiving Chemotherapy: ASCO Guideline for Geriatric Oncology” [1], which called for the development of detailed, evidence- and/or consensus-based GA tools, and interventions for rehabilitation, improvement of nutritional state, and adjustment of concomitant drugs. In Japan, GA is not currently performed in clinical practice because there is no standard method for performing GA, it takes considerable time, and there is little evidence of its usefulness in making decisions regarding cancer treatment [2]. Older cancer patients are currently not administered individualized treatment, and they may be either under- or over-treated [3]. To improve the current situation, there is a need to develop a simple system for performing GA, establish a GA environment, and determine the usefulness of GA in clinical practice. Therefore, we plan to conduct a study (ENSURE-GA) of GA in older patients with lung cancer to evaluate whether performing GA along with intervention improves patient satisfaction with their treatment. We believe that the study findings will improve the penetration rate of GA assessment in Japan and promote the provision of personalized medicine to older patients with cancer.

## Methods

### Study objective, design, and setting

The primary objective of the ENSURE-GA study is to evaluate the effect of an intervention based on a standardized GA on patient satisfaction with their treatment. This study will be a phase III comparative clinical trial with a cluster-randomized design and will be conducted in 81 medical facilities that have been selected based on the following four factors: (i) number of beds ( ≧ 200 beds or < 200 beds); (ii) whether or not designated as a cancer hospital by the Japanese Ministry of Health, Labor, and Welfare; (iii) region (divided into 6 regions, and these regions were evenly allocated with participating facilities from each region); and (iv) whether GA is usually included in medical treatment. Each facility will be randomly allocated in order of enrollment to the intervention or non-intervention group in a 1:1 ratio.

The primary endpoint will be the change in patient satisfaction according to the Health Care Communication Questionnaire (HCCQ) questionnaire between the GA and 3 months later. The secondary endpoints will be (i) the change in the quality of life; (ii) the treatment completion rate; (iii) the proportion of participants showing improvement by at least one grade in their Eastern Cooperative Oncology Group performance status (ECOG-PS); (iv) the relationship between the pre-chemotherapy risk assessment results and adverse events, evaluated separately for cytotoxic anticancer agents, molecular-targeted agents, and immune checkpoint inhibitors; and (v) the proportion of screened patients who had vulnerability factors in at least one of the GA tools and are enrolled in the study.

We have built a GA tool as an iPad application and have developed a system that displays GA results and recommendations for related interventions. Using this system, GA is performed for each participant. In the intervention facilities, participants’ GA results and the intervention method recommended on the basis of these results will be displayed immediately on the iPad in the form of a report. Using this report, the responsible physician will explain the GA results and the intervention method to the participant (Table 1). In the non-intervention facilities, the physician will perform a GA, but the results and the intervention method recommended based on these results will not be displayed on the iPad. The physician will decide on treatment solely on the basis of the ECOG-PS and multiple-organ function, as is currently the standard for lung cancer treatment in Japan. Patients who are analyzed for the primary endpoint are those with one or more vulnerability factors identified using the GA tools. All participants will complete a patient satisfaction survey before treatment initiation and 3 months later (Fig. 1). The ENSURE-GA study is an intergroup trial, and the North East Japan Study Group and CS-Lung are working together to conduct the trial.

**Table 1 Tab1:** Geriatric assessment tools and examples of possible interventions based on the assessment results

Evaluated items	Recommended GA tools	Example of intervention (support) method based on the GA results
Physical function: Falls	• Lawton IADL • “How many times have you fallen during the last 6 months?”	• Referral to an occupational therapist and/or physiotherapist • Prevention of falls • Evaluation of safety of home and garden
Complications, polypharmacy	• CCI • Number of drugs in regular use	• Encouraging involvement of family members in management of complications • Collaboration between the primary-care physician and a geriatrician • Consulting a pharmacist regarding reducing the number of medications
Cognitive function	• Mini-Cog	• Evaluation of decision-making capability • Selection of someone with power of attorney, if necessary • Collaboration between a geriatrician and a cognitive function specialist • Prevention of delusions, by adjusting medication
Depressive state	• GDS	• Referral to a psychiatrist • Promoting participation in social activities • Prescription of an antidepressant
Nutrition	• BMI below 21 kg/m^2^	• Referral to a dietician • Provision of support for preparing meals
Social support	• Do you have key persons, family, or friends regarding cancer treatment?	• Referral to a social worker

*BMI* body mass index; *CCI* Charlson Comorbidity Index; *GA* geriatric assessment; *GDS* geriatric depression scale; *IADL* Instrumental Activities of Daily Living Scale; *Mini-Cog* Mini-Cog screening for cognitive impairment in older adults

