### Inclusion and exclusion criteria

Participants will be required to meet all of the following inclusion criteria:

histologically and/or cytologically confirmed to have non-small-cell lung cancer,radical resection-radiotherapy and radical chemotherapy are not feasible,age at least 75 years,ECOG-PS of 3 or less, and.provide informed consent for participation.

Patients with any of the following factors will be excluded from the study:

dementia and aggressive cancer treatment,psychiatric disorders that could interfere with participation, and.study participation is judged by the responsible physician to be inappropriate for any other reason.

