### Statistical analysis

A mixed-effects model will be used to perform intergroup comparisons taking intra-cluster correlation into consideration, and the 95 % confidence interval will be calculated. Statistical analyses are performed using the Statistical Analysis System, version 9.4 (SAS Institute Inc., NC, USA).

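### Secondary endpoint (iii) counts PS 0 patients, who cannot improve, as non-improvers; this shrinks the absolute difference, and a different PS mix between arms could bias it

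*Protocol article*

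**What the plan says.** Under Study objective, design, and setting, the third secondary endpoint is "the proportion of participants showing improvement by at least one grade in their Eastern Cooperative Oncology Group performance status (ECOG-PS"). Under Inclusion and exclusion criteria, the only performance-status condition is "ECOG-PS of 3 or less"; there is no lower limit, so grades 0 to 3 are eligible.

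One analysis-set restriction is stated: "Patients who are analyzed for the primary endpoint are those with one or more vulnerability factors identified using the GA tools". It concerns the primary endpoint and is based on geriatric vulnerability, not on performance status.

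On allocation: "Each facility will be randomly allocated in order of enrollment to the intervention or non-intervention group in a 1:1 ratio". The four facility factors listed there (beds, cancer-hospital designation, region, usual use of GA) do not include patient performance status.

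On analysis: "A mixed-effects model will be used to perform intergroup comparisons taking intra-cluster correlation into consideration". Covariates are not discussed.

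**The concern.** PS 0 is the best grade, so a patient who starts there cannot improve by a grade. Taken with the eligibility rule, the endpoint puts such patients in the denominator with a fixed outcome of no improvement.

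Two things follow. First, the proportion measures partly the intervention and partly the baseline PS mix. The larger the PS 0 share, the smaller the absolute difference that a given benefit in PS 1–3 can produce, and the lower the power to see it. Second, if the arms enrol different PS mixes, the proportions differ even when the intervention does nothing. Facilities rather than patients are randomized, and the GA report appears on the iPad only at intervention facilities, so site staff will know their arm. Patient-level balance in PS is therefore less secure than under individual, concealed allocation.

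**Working it through.** **The plan's own figure.** The article states no power for the ECOG-PS endpoint. Its sample size is for the HCCQ score and reproduces:
- Per arm: 2 × 4.5² × (1.96 + 0.842)² / 1.1² = 262.7, so 263, or 526 in total, as stated.
- Design effect: 1 + (15 − 1) × 0.05 = 1.70. Then 526 × 1.70 = 894.2, and 894.2 / 15 = 59.6 clusters. The article says this "yields a value of 895 for *n’*, and a required number of clusters of 60", which agrees to rounding.

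**Inputs for the ECOG-PS endpoint**
- From the article: N = 1020; 81 sites, so the mean cluster size is 1020 / 81 = 12.6.
- Borrowed from the HCCQ calculation: ICC 0.05.
- Assumed, because the article gives no figure: PS 0 share *s* of 10% to 40%; improvement in PS 1–3 of 20% vs 30%.

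**Dilution.** Rate in all participants = (1 − s) × rate in PS 1–3. The difference is multiplied by (1 − s). In the risk ratio the factor cancels, so it stays at 30 / 20 = 1.5.

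**Power.** Φ(d / SE − 1.96), with SE = √{[p₁(1 − p₁) + p₂(1 − p₂)] / n_eff}.
- All participants: design effect 1 + 11.6 × 0.05 = 1.58; n_eff = 510 / 1.58 = 323 per arm.
- PS 1–3 only: the patients per site fall too, so the cluster size is 12.6 × (1 − s) and the design effect is recalculated.

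Worked example at s = 25%:
- All: 15% vs 22.5%; SE = 0.0306; Φ(0.075 / 0.0306 − 1.96) = 68.9%.
- PS 1–3: cluster size 9.45; design effect 1.42; n_eff = 510 × 0.75 / 1.4225 = 269; SE = √(0.37 / 269) = 0.0371; Φ(0.10 / 0.0371 − 1.96) = 76.9%.

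| PS 0 share | Difference, all | Power, all | n_eff per arm, PS 1–3 | Power, PS 1–3 |
|---|---|---|---|---|
| 10% | 9.0 points | 79% | 303 | 82% |
| 25% | 7.5 points | 69% | 269 | 77% |
| 40% | 6.0 points | 57% | 230 | 70% |

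The difference in PS 1–3 is 10 points throughout. If the design effect were held at 1.58 after removing PS 0 patients, power in PS 1–3 at s = 25% would be 72.5% (242 per arm). That understates the gain, because removing patients makes the clusters smaller.

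**Imbalance without any effect.** False difference = rate in PS 1–3 × difference in PS 0 share. Assume 25% improvement in PS 1–3 in both arms and PS 0 shares of 20% vs 30%:
- 0.25 × 0.80 = 20.0% vs 0.25 × 0.70 = 17.5%, a false difference of 2.5 points.
- SE = √[(0.20 × 0.80 + 0.175 × 0.825) / 323] = 0.0307, so the chance of p < 0.05 in that direction is Φ(0.025 / 0.0307 − 1.96) = about 13%, against a nominal 2.5%.

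**How likely is such an imbalance by chance?** With 25% PS 0 overall and the same ICC, the SD of the difference in PS 0 share is √(2 × 0.25 × 0.75 / 323) = 3.4 points. A 10-point gap is 10 / 3.4 = 2.9 SD, so it would need differential recruitment rather than chance.

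**The case against.** The strongest reply is that this is a one-clause entry in a list of secondary endpoints in a condensed article. It says participants, not all participants. The evaluable set and the covariates may be settled in the full protocol or SAP. That stands as far as the covariates go: a reader might infer from the Statistical analysis section that no baseline-PS adjustment is planned, but silence in two sentences does not show that. It does not dispose of the definition. The article fixes the numerator, the population and the eligibility range, and nothing in it removes PS 0 patients.

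A second reply is that a responder proportion over everyone enrolled is a legitimate population-level quantity and keeps all patients. That is true, and on the ratio scale nothing is diluted. The cost is to the absolute difference and to power.

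A third reply concerns bias. A reader might infer that any PS imbalance produces a spurious finding. The document does not support that: chance imbalance is part of the sampling error and does not inflate the type I error. Bias requires a systematically different PS mix by arm, for which the article gives no figure. Knowledge of the arm at the sites makes it possible, not shown.

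Finally, restricting to PS 1–3 would not by itself remove such a bias, since the mix of grades 1, 2 and 3 could differ as well. This stands, and it makes baseline-PS adjustment the essential part of the remedy.

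**Conclusion.** The point holds as a minor weakness in how a secondary endpoint is defined. No figure in the article is wrong and no two passages contradict each other; the endpoint and the eligibility rule simply fit together badly.

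Under the assumptions above, counting PS 0 patients costs about 3, 8 and 13 percentage points of power at PS 0 shares of 10%, 25% and 40%. These figures depend on assumed improvement rates and on an ICC taken from a different outcome, so they show the order of magnitude only. The bias is conditional on differential recruitment and is small in the example: 2.5 points for a 10-point gap in PS 0 share. It would be too strong to say that the endpoint is biased as it stands, or that the trial's main conclusion is at risk.

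**What to change.** Either of two changes would do.

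1. Analyse 3-month ECOG-PS as an ordinal outcome in all participants, using a mixed-effects model with a site effect and adjustment for baseline PS. PS 0 patients then contribute, because they can stay the same or worsen. The result is a shift in the PS distribution rather than a proportion improved, and the usual form of the model assumes proportional odds.
2. Keep the responder proportion, define it among participants with baseline ECOG-PS 1–3, and include baseline PS in the mixed-effects logistic model. The adjustment should not be left out, for the reason given above. PS 0 patients leave this endpoint, and membership of the analysis set rests on a baseline grade that may be recorded by staff who know the arm.

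The first option avoids selecting patients on baseline PS. Reporting the baseline PS distribution by arm would let readers judge the recruitment question under either. The cost is a line or two of endpoint and model wording. Any change-in-PS endpoint already needs baseline PS, so no new data are required, and the primary endpoint and sample size do not change. (The article gives no time point for this endpoint; 3 months is taken from the primary endpoint.)
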